## 3. Discussion

The purpose of the present study will be to evaluate the effect of a combined training program in older adults with PD. In particular, the proposed 12-week training program will aim to improve postural control and fine motor coordination in mild to moderate PD subjects.

PD is commonly considered as a form of “accelerated aging” of the nervous system affecting subjects’ ability to control movements with tremor disorders [36,37]. The major characteristics of PD are impairments in movement while resting or moving, rigidity [36] and more difficulties in executing simultaneous movements and sequential tasks with respect to simple ones [5]. In particular, the progression of PD leads to a phenomenon called festination, resulting in a decrease in gait speed and an increase in the rate of falls with a consequent loss of independency [5]. Moreover, several studies have reported the negative association between fine motor skills, especially hand disability, and cognitive dysfunction in the PD population [38,39]. In fact, the dopamine neuron depletion caused by PD influences various domains of executive functions, motor coordination and psychomotor speed [40]. These functional disabilities compromise the regular daily activities required for dressing, ascending or descending steps, to self-take care and/or walking. Therefore, the implementation of training interventions to improve postural control and fine motor coordination in PD subjects is fundamental.

Studies proposed several kinds of training programs to improve these abilities in subjects with PD. In the last decade, evidence supported dance activities, aquatic-based exercise and oriental disciplines as effective symptom management modalities. It emerged, in fact, that dance classes could improve functional abilities [41], quality of life [42] and activities of daily living in a PD population [43]. About oriental disciplines, Tai Chi resulted in promising gains in mobility and balance, and it was demonstrated to be safe and popular among subjects with PD at an early stage of the disease [44]. Furthermore, aquatic exercise improves the motor impairments of PD, and it seems to achieve greater benefits than land-based exercise on balance capacity, fear of falling and health-related quality of life in PD populations with a mild to moderate degree of disability [45].

On the other hand, among different single training protocols, combined exercise programs (postural control and fine motor skills exercises) might be more effective. In fact, intervention protocols including several physical activities such as multidirectional stride training, climbing and descending, stretching forward and sideways, obstacles, turning around, stepping, getting up and sitting down, specific trunk rehabilitation exercises, passive spinal joints mobilization, writing, drawing, bouncing a ball during gait, maintaining balance while standing on stable and unstable support bases of different consistency and walking with open or closed eyes are commonly used approaches, which show improvements in muscle activation, fine coordination and postural control and decrease the risk of falls [19,20,21,22,23,46,47].

In line with such evidence, we hypothesized that different performances between groups will expected: (1) no significant differences between PD and CON group for WB and GPT test values before the beginning of the training intervention (PRE-intervention); (2) significantly better WB and GPT test values in PD subjects after the training intervention (POST-intervention) when compared to the base values (PRE-intervention); and (3) no significant differences in WB and GPT test values in CON subjects after the training intervention (POST-intervention) when compared to the base values (PRE-intervention). Therefore, thanks to the future findings of the present study, health professionals could provide individualized training protocols to improve postural control, fine motor skills and perform a regular level of physical activity [24]. Moreover, WB and GPT tests could be practical, inexpensive, administrable and accurate tools to provide essential and useful information about the evaluation of postural control and fine motor skills, especially in light of the progressive degenerative course of PD.

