## Abstract

Parkinson’s disease (PD) is a progressive and neurodegenerative disorder defined by physical symptoms such as hand disability and postural instability. To counteract the detrimental effects of PD, physical activity programs showed improvements in overall aspects of physical functioning. Therefore, this protocol will aim to evaluate the effect a of postural and fine motor skills training program in older adults with PD. PD individuals, with mild to moderate stage PD, aged between 65 to 80 years, will be voluntary selected from the Nursing Home Residences and Rehabilitation Centers. Subsequently, they will be randomly assigned to intervention group (PD) to receive a combined training program (postural control and fine motor skills exercises) or to the Control group (CON) to receive a stretching program. Before (PRE) and after (POST) a 12-week program both groups will perform wobble board (WB) and grooved pegboard (GPT) tests. Different performances between groups will be expected: (1) no significant differences between PD and CON group for WB and GPT test values before the beginning of the training intervention (PRE); (2) significantly better WB and GPT test values in PD subjects after the training intervention (POST) when compared to the base values (PRE); and (3) no significant differences in WB and GPT test values in CON subjects after the training intervention (POST) when compared to the base values (PRE). The findings of the present study protocol could be used for future studies investigating clinical populations, such as PD, and the effects of different rehabilitative interventions aiming to improve postural control and fine motor skills performances assessed by WB and GPT tests.

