#### 2.2.6. Statistical Analysis

To ensure confidentiality and protection of personal data, subjects’ data will be de-identified indicating a numerical code for each participant.

The ‘Intervention’ will be considered as an independent variable, whereas WB and GPT will be considered as dependent variables. The collected data for the analysis of WB and GPT will be expressed in time in seconds (s). Means and SDs will be calculated for each variable. The normal distribution of data will be assessed by the Shapiro–Wilk test. If data are normally distributed, parametric statistical analysis (Analysis of Variance (ANOVA) for repeated measures) will be performed. If data are not normally distributed, non-parametric statistical analysis (Kruskal–Wallis ANOVA for ranked data) will be performed. Therefore, the appropriate analysis will be used to test for differences between PD and CON groups over time (PRE and POST).

In line with previous research, statistical significance will be set at a level of *p* < 0.05. The data will be analyzed using STATA 15 (StataCorp LP, College Station, TX, USA). In addition, the intervention will be considered effective if the evaluated variables (WB and GPT) show improvements in the PD group compared to the CON one.

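### The three stated hypotheses never compare change between the arms, so they do not match the between-arm analysis and effectiveness criterion of section 2.2.6

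*Protocol article*

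**What the plan says.** Both arms consist of people with Parkinson's disease. The protocol calls the combined-training arm PD and the stretching arm CON.

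The Abstract introduces its expectations with "Different performances between groups will be expected". The Discussion (section 3) repeats them as three numbered hypotheses.

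- Hypothesis (1) sets the two arms against each other, but only at baseline: "no significant differences between PD and CON group for WB and GPT test values before the beginning of the training intervention (PRE-intervention").
- Hypothesis (2) looks inside the PD arm alone. It expects "significantly better WB and GPT test values in PD subjects after the training intervention (POST-intervention"), judged against that arm's own starting level.
- Hypothesis (3) looks inside the CON arm alone. It expects "no significant differences in WB and GPT test values in CON subjects after the training intervention (POST-intervention"), again judged against that arm's own starting level.

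Section 2.2.6 (Statistical Analysis) takes a different line. It will "test for differences between PD and CON groups over time (PRE and POST"), by repeated-measures ANOVA or a rank-based alternative, and "statistical significance will be set at a level of *p* < 0.05". It then gives the only explicit criterion for success: the intervention counts as effective if the outcomes improve in the PD arm relative to the CON arm.

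Two other places bear on the point. Section 2.2.4 (Intervention) justifies stretching as the control partly because it helps physical aspects of the disease, balance and motor coordination among them. Section 2.2.2 (Sample Size) sets 15 subjects per group as the recruitment goal of a pilot study, from which an effect size is to be estimated. It gives no assumed effect.

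**The concern.** The hypotheses are announced as differences between groups, but the only between-group item is (1), which concerns baseline. Items (2) and (3) are separate PRE-POST statements inside each arm. Whether combined training does better than stretching, the question that randomisation can answer, is not among them.

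The difference between a significant and a non-significant result is not itself a test. If both programmes help equally, chance alone will often make one arm cross p < 0.05 and leave the other short of it. Item (3) also reads a non-significant result in a small arm as absence of change.

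Equal or partial improvement in the control arm is realistic here, because section 2.2.4 itself credits stretching with benefit on balance and motor coordination, the domains the trial measures. A reader who holds the results against the hypotheses as written could take an improvement common to both arms for an effect of the combined programme. That reader could also count the trial as failing (3) when the training arm clearly improved more.

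**Working it through.** **Side by side**

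| Statement | Arms compared | Time points |
|---|---|---|
| Hypothesis (1) | PD vs CON | PRE only |
| Hypothesis (2) | within PD | PRE vs POST |
| Hypothesis (3) | within CON | PRE vs POST |
| Section 2.2.6 analysis | PD vs CON | over PRE and POST |
| Section 2.2.6 effectiveness criterion | PD relative to CON | improvement |

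The last two rows have no counterpart among the hypotheses.

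**Inputs**

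- n = 15 per arm: the pilot recruitment goal in section 2.2.2.
- Significance level 0.05: section 2.2.6. Two-sided is an assumption, since the protocol does not say.
- Standardised change d (true mean PRE-POST change divided by the SD of change scores): assumed, as the documents give none.
- One outcome, normal change scores, independent arms with equal SD, paired t-test within each arm: assumptions.

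The protocol states no power or effect size, so there is no figure of its own to reproduce.

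**Formula.** Let p be the chance of a significant improvement in one arm and q the chance of any significant change. With the same d in both arms,

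P(PD significantly better and CON not significant) = p(1 − q).

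The chance of a significant worsening is negligible for the values of d used here, so this is close to p(1 − p). That expression has its maximum at p = 0.5, where it equals 0.5 × 0.5 = 0.25, whatever the sample size.

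**Results at n = 15.** Here p comes from the noncentral t distribution with 14 df and noncentrality d√15.

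| d, both arms | p | p(1 − q) |
|---|---|---|
| 0.3 | 0.190 | 0.154 |
| 0.5 | 0.438 | 0.246 |
| 0.7 | 0.713 | 0.205 |

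The ceiling of 0.250 is reached near d = 0.54. In the same scenarios a between-arm test of the change rejects in favour of PD 2.5% of the time, because the true difference is zero. Simulation with 200,000 trials per scenario confirmed both: at d = 0.55 the pattern appeared in 24.9% and the between-arm test favoured PD in 2.5%. At d = 0.5, about 90% of the trials showing the pattern had no significant between-arm difference.

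**The other direction.** Suppose the true changes are 1.5 in PD and 0.5 in CON (again assumed). PD is significant almost always (p > 0.999) and CON reaches significance with probability 0.438. The hypothesised pattern therefore appears with probability about 1 − 0.438 = 0.562. The between-arm test has 28 df and noncentrality (1.5 − 0.5) × √(15/2) = 2.74, which gives power 0.753.

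**Sensitivity to n.** The pattern probability p(1 − q) at other sample sizes:

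| d | n = 15 | n = 30 | n = 50 |
|---|---|---|---|
| 0.3 | 15.4% | 22.9% | 24.8% |
| 0.5 | 24.6% | 18.6% | 6.2% |
| 0.7 | 20.5% | 3.9% | 0.2% |

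**Two outcomes.** At n = 15 and d = 0.55, with an assumed correlation between wobble board and pegboard of 0 to 0.8, the pattern appears on both outcomes in 6% to 15% of trials. It appears on at least one in 43% to 34%.

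**The case against.** The strongest reply is that the decision is already made between arms. Section 2.2.6 plans a comparison of PD with CON over time, and its effectiveness criterion is improvement in PD relative to CON. A reader might infer from the hypotheses that the trial plans no between-arm comparison, or that it has a second decision rule under which effectiveness is declared when PD is significant and CON is not. The documents support neither. The three items are stated as expectations, and no section says that meeting (2) and (3) establishes effectiveness. This part of the reply stands, and it limits the point to a mismatch between hypotheses and analysis.

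The reply is also right about the numbers. Fifteen per arm is a pilot goal and not the size of a later trial, the values of d are not the protocol's, and 25% is a ceiling for one outcome. If the pattern is required on both outcomes the figure falls; if either suffices it rises.

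A reader might also object that (2) credits training with practice gains. That adds little: (2) asserts improvement from baseline without attributing all of it to training, and the comparison with CON in section 2.2.6 guards against a practice effect shared by both arms.

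Finally, within-arm tests are common follow-ups to a repeated-measures ANOVA, and forbidding them would be a preference. Reporting them is acceptable provided they do not carry the conclusion.

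The mismatch itself remains. The published hypotheses are what the results will be read against, and they can point the opposite way from the criterion in section 2.2.6. That criterion names no contrast or threshold, so it does not by itself rule out reading a PD improvement beside a CON non-improvement as success.

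**Conclusion.** The concern holds as an inconsistency: no hypothesis in the Abstract or Discussion states the between-arm difference in change on which section 2.2.6 bases its analysis and its judgement of effectiveness. Taken as evidence of a difference between arms, the hypothesised pattern would mislead in up to one trial in four for a single outcome when the arms improve equally. The corresponding rate for a between-arm test is 2.5%.

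The ceiling depends on independent arms with the same n, the same SD and the same true change, but not on n itself. The figures of 15%, 25% and 20% also depend on 15 per arm and on the assumed effects.

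Severity: should be fixed. The planned analysis already points the right way, so the hypotheses need to be brought into line with it; the design does not need to change.

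**What to change.** In the Abstract and the Discussion, replace hypotheses (2) and (3) as the basis for the conclusion with one hypothesis per outcome: the PRE-to-POST change differs between the combined-training and stretching arms.

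In section 2.2.6, name the between-arm (group-by-time) contrast as the test of that hypothesis, report it as a difference with a 95% CI, and state that this contrast alone decides effectiveness. Within-arm PRE-POST results may stay as secondary description, with a sentence saying that they do not support a claim of effectiveness.

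The cost is rewording the hypothesis paragraphs in the Abstract and Discussion and adding a few sentences to section 2.2.6. No new data, visits or participants are needed. The one downside is that the within-arm results lose their headline place.

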### 2.2. Procedures

#### 2.2.1. Preliminary Evaluations

One week before the testing session, subjects’ characteristics will be assessed. Body mass and height will be measured by means of a scale with integrated stadiometer with a precision of 0.1 kg and 0.1 cm (Seca, model 709, Vogel & Halke, Hamburg, Germany), and body mass index (BMI) will be calculated [31]. Waist circumference will be measured at the narrowest part of the abdominal region (if the narrowest part of the abdominal region is not clearly distinguishable, the waist will be measured midway between the 10th rib and the crest of the pelvic bone); hip circumference will be measured horizontally at the most protruding points in back of the gluteal region, side and front. Waist to hip ratio (WHR) will be calculated.

Subsequently, subjects will be recruited for the single-blind study and randomly allocated in two groups: PD group and Control group (CON group). PD group will participate in the combined training program; CON group will participate in a stretching program. Before (PRE) and after (POST) the combined training program (intervention) both groups will perform the tests (described in Section 2.2.3) in a randomized order. Participants in both groups will be instructed to continue with their usual care and advised not to change their daily activities during the trial. All the assessments will be carried out when participants will be in the ‘‘on’’ phase (i.e., when medications will be working and symptoms controlled).

Subjects will be able to withdraw from the study at any time for any reason without any consequences.

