#### 2.2.2. Sample Size

For the calculation of sample size, no a priori hypothesis was established due the lack of previous data regarding combined exercise program (postural control and fine moto skills) in subjects with PD. For this reason, a pilot study will be performed to estimate the effect size (ES) of the intervention. The pilot study’s recruitment goal will be 15 subjects with PD for each group. Therefore, the ES, using Cohen’s d, based on the results of the pilot study, will be determined. In line with similar research, an ES value less than 0.2 will considered trivial, from 0.2 to 0.5 small, greater than 0.5 to 0.8 moderate and greater than 0.8 large [32].

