#### 2.2.4. Intervention

For 12 weeks, the PD group will receive at least one 60-min session twice a week of a supervised combined training program performed in the participating facilities. The PD group will perform a combined training program (balance and fine motor skills exercises), while the CON group will perform a stretching program. The stretching program will be adopted because of its positive applications in social and emotional aspects, in integrating real tasks from daily life activities and in improving overall physical aspects such as tremor, rigidity, bradykinesia, balance and motor coordination impairments, characterizing PD disease [34].

-PD group

The exercise sessions will include a 10-min warm-up and a cool-down of 5-min of walking, joint mobility (for upper and lower limbs) exercises in clockwise and counterclockwise circling and breathing exercises and followed by 45 min postural control training. After each exercise, subjects will perform a 1-min break in a comfortable seated position.

For postural control training, progression during the intervention period will be reached. For example, visual information will be trained by closing the eyes or looking up, down and sideward; proprioceptive system will be elicited using different unstable surfaces with respect to stable platforms and vestibular system will be disturbed using music or inhibited with appropriate earphones to isolate subjects from the external setting.

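### The three stated hypotheses contain no between-arm comparison of change and do not match the effectiveness criterion in section 2.2.6

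*Protocol article*

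**What the plan says.** Section 3 (Discussion) lists three hypotheses, and the Abstract gives the same three almost word for word:

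1. At baseline: "no significant differences between PD and CON group for WB and GPT test values before the beginning of the training intervention (PRE").
2. Within the training arm: "significantly better WB and GPT test values in PD subjects after the training intervention (POST-intervention) when compared to the base values (PRE-intervention").
3. Within the stretching arm: "no significant differences in WB and GPT test values in CON subjects after the training intervention (POST-intervention) when compared to the base values".

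Section 2.2.1 says that participants are "randomly allocated in two groups: PD group and Control group (CON group"). Both arms consist of people with Parkinson's disease; "PD group" is the label of the training arm.

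Section 2.2.6 plans a repeated-measures ANOVA, or a Kruskal–Wallis ANOVA if the data are not normal, to look for differences between the two groups over time. It counts the intervention as effective if WB and GPT "show improvements in the PD group compared to the CON one". It names no group-by-time term and does not link this criterion to the three hypotheses.

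Section 2.2.4 justifies stretching as the control partly by its value "in improving overall physical aspects such as tremor, rigidity, bradykinesia, balance and motor coordination impairments".

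**The concern.** The hypotheses are introduced as expected differences in performance between groups, but none states such a difference in change or at POST. Hypothesis 1 concerns a baseline difference that, under randomisation, can arise only by chance. Hypotheses 2 and 3 set a significant within-arm result beside a non-significant one. That does not show that the arms differ, and a non-significant change in about 15 people does not show that there was no change.

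Two errors become possible if conclusions follow the hypotheses. A change common to both arms, from repeating the tests or from any exercise, could be reported as an effect of the training. Conversely, a real advantage over stretching could be reported as a failed hypothesis because the control arm also improved, which is what section 2.2.4 gives reason to expect.

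**Working it through.** **Hypotheses against the criterion.**

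| Statement | Comparison made | Between-arm difference in change? |
|---|---|---|
| Hypothesis 1 | PD v CON at PRE | No |
| Hypothesis 2 | PRE v POST within PD | No |
| Hypothesis 3 | PRE v POST within CON | No |
| Section 2.2.6 criterion | PD improvement relative to CON | Yes, but contrast not named |

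The criterion can be met while hypothesis 3 fails, and hypotheses 1–3 can all hold without a significant between-arm difference.

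**Inputs.** The plan gives no error rate or power for this point, so there is no figure to reproduce.
- Significance level: "statistical significance will be set at a level of *p* < 0.05" (section 2.2.6). Sidedness is not stated; two-sided is assumed.
- Sample size: "The pilot study’s recruitment goal will be 15 subjects with PD for each group" (section 2.2.2). This is a pilot goal, not a final sample size; 15 completers per arm are assumed.
- Within-arm standardised change, dz = mean change / SD of change: not given, so taken from 0 to 1.0.
- Assumed: normal data, equal variances, a paired t-test within each arm, and the same true change in both arms (no benefit over control).

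**Formula.** Let p be the probability that one arm's paired t-test (14 df, noncentral t) shows significant improvement. The arms are independent, so P(PD significantly better, CON not significant) ≈ p(1 − p), which cannot exceed 0.25. The table also subtracts the small probability that CON is significantly worse; this is visible only at small dz.

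| dz, both arms | p | P(pattern), one outcome |
|---|---|---|
| 0 | 0.025 | 0.024 |
| 0.2 | 0.108 | 0.096 |
| 0.3 | 0.190 | 0.154 |
| 0.5 | 0.438 | 0.438 × 0.562 = 0.246 |
| 0.54 | 0.495 | 0.250 (maximum) |
| 0.8 | 0.821 | 0.821 × 0.179 = 0.147 |
| 1.0 | 0.949 | 0.949 × 0.051 = 0.048 |

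**Variants at the peak** (simulation, 40,000 runs per setting, PRE–POST correlation 0.5 or 0.8, treating WB and GPT as one variable each):
- hypothesis 1 also required: about 23–23.5%;
- pattern required on both WB and GPT: about 6% if uncorrelated (0.25² = 0.0625), about 10% at correlation 0.5;
- pattern accepted on either: about 39–44% (uncorrelated: 1 − 0.75² = 0.4375).

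**Between-arm test of change, same settings:** about 5% two-sided, of which about 2.5% favours PD, whatever the common change. At the peak, about 90% of runs showing the one-outcome pattern have no significant between-arm difference favouring PD.

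**The opposite error.** Hypothesis 3 fails when the CON change is significant, however large the advantage of training. From the column for p, a true CON improvement of dz = 0.5 makes it fail in about 44% of trials, and dz = 0.8 in about 82%.

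**The case against.** A reader might infer that the protocol will credit a useless programme up to a quarter of the time. The documents do not support that. Section 2.2.6 states when the programme counts as effective, and the statement is comparative; the planned analysis is also described as PD against CON over time. Nowhere does the protocol say that efficacy follows from PD being significant and CON not. Paired t-tests within arms are not in the analysis section either. The hypotheses may simply describe an expected pattern. The 25% is therefore the single-outcome worst case of a rule the protocol does not adopt, at one particular size of common change. The hypotheses speak of WB and GPT together, which points to the lower 6–10% peak.

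A reader might also infer that a baseline significance test is planned. Section 2.2.6 plans none and attaches no consequence to one.

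Nor do the documents quantify practice gains. Section 2.2.3 provides free practice and familiarisation, which should limit them, and testing is separated by a 12-week programme. The firmer ground for a common change is the protocol's own rationale for stretching.

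Finally, with two time points the group-by-time term of the planned ANOVA is already a valid treatment comparison, so ANCOVA is an improvement and not a necessity.

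All of this stands and limits the size of the point. It does not remove the mismatch. Section 2.2.6 never names the group-by-time term. Its rank-based fallback compares independent groups on one factor, so it tests between-arm change only if applied to change scores, which the section does not say. Improvement compared with CON can then still be read as the pattern in hypotheses 2 and 3.

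**Conclusion.** The point holds as a mismatch in the stated text. The only hypotheses contain no between-arm comparison of change, they do not correspond to the criterion in section 2.2.6, and hypothesis 3 conflicts with the rationale for the control in section 2.2.4.

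Its numerical consequence is conditional. If the pattern in hypotheses 2 and 3 were used to judge efficacy, the false-credit rate per outcome would run from about 2.4% with no common change to 25% at worst, with a peak of about 6–10% if both outcomes must show it. The direct comparison gives about 2.5% favouring PD. The 25% ceiling does not depend on sample size, but the dz at which it occurs does; 0.54 belongs to 15 per arm. The results rest on the assumptions listed with the inputs, chiefly equal true change in both arms and a range of dz that the documents do not supply.

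Because the hypotheses determine what the trial will claim, they should be aligned with the criterion before any data are analysed.

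**What to change.** In the Abstract and section 3, replace the three hypotheses with one per outcome: mean POST performance, adjusted for PRE, is better in the training arm than in CON. In section 2.2.6, name the matching estimate, the ANCOVA arm effect with its 95% confidence interval, as the basis of the effectiveness criterion.

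The group-by-time term of the planned ANOVA would be a valid alternative, but it is usually less precise. With equal variances and PRE–POST correlation ρ, the ratio of the ANCOVA variance to that of the change-score comparison is approximately (1 − ρ²) / [2(1 − ρ)] = (1 + ρ)/2. That is 0.75 at ρ = 0.5 and 0.90 at ρ = 0.8, both assumed values.

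Report baseline values and within-arm changes descriptively, and base no efficacy conclusion on them. Reconcile the expectation for CON with the rationale in section 2.2.4.

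The cost is rewording and a minor change of model. No new measurements or participants are needed, since PRE and POST are already collected in both arms.
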